## **2.17 Responsibilities**

The responsibilities designated to each member of the research team are documented on the Delegation of Authority Form. A delegated staff member who is properly trained will be responsible for the informed consent process, review for eligibility, questionnaire administration, data entry, PA programme administration, and e-CRF entries.

## **2.18 Safety/Harms**

### **2.18.1 Safety of PA**

There may be the possibility of injury while participating in PA. Serious inherent risks are rare but include cardiac events and musculoskeletal injuries. To reduce the risk of sustaining any injuries, the PAR-Q will be completed at screening and the PA program will be completed under the supervision of a program trainer who is a certified PA trainer with a background in exercise and health psychology. Participants are not required to perform any exercise that is deemed uncomfortable and will be instructed to not continue to exercise if the participant experiences sharp pain, nausea, dizziness, or light-headedness. The PA program is individualized and tailored to the needs and capabilities of each participant which limits the risk of injury.

### **2.18.2 AE definitions**

**AE:** An AE is any untoward medical occurrence in a study participant receiving the PA programme and which does not necessarily have a causal relationship with this treatment. An AE can therefore be any unfavorable and unintended sign (including an abnormal laboratory finding), symptom, or disease temporally associated with the use of an investigational medical product (IMP), whether or not related to the IMP.

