|--|-----------------------------------------------------------------------------------------------------------------------------------------------------------------------------------------------------------------------------------------------------------------------------------------------------------------------------------------------------------------------------------------------------------------------------------------------------------------------------------------------------------------------------|---------------------------------------------------------------------------------------------------------------------------------------------------------------------------------------------------------------------------------------------------------------------------------------------------------------------------------------------------------------------------------------------------------------------------------------------------------------------------------------------------------------------------------------------------------------------------------------------------------------------------------------------------------------------------------------------------------------------------------------------------------------------------------|

**Note:** X = the CONMED and AE log will occur during the supervised PA session for participants randomized to the PA group; participants in the TAU group will instead receive a weekly phone call. X = will occur once at the Exit Visit with Oura Ring drop off. X = optional qualitative interview to occur any time during study. X = the qualitative interviews will occur once during the 6-week follow-up period.

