## 2.10 Allocation

If potential participants meet the eligibility criteria, they will be enrolled in the trial and will be randomized in a 2:1 allocation to receive a PA program add-on (experimental group) or TAU (control group). Thus, 20 participants will be randomized to the PA group and 10 participants will be randomized to the TAU group. Block randomization will be computer-generated, and the sample will be stratified for sex given the potential for differences in response in these groups. The randomization schedule will employ random permuted blocks of varying sizes. It will be administered by a member of the study staff.

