It is important to note that participants will obtain the Oura Ring during the in-person baseline visit and will begin using it immediately, approximately 3 weeks prior to the start of the intervention period, to establish participants' baseline parameters. Participants will consistently use the Oura Ring for a total of approximately 13 weeks (i.e., during the ~3 weeks of baseline, during the 4 weeks of the intervention period, and during the 6-weeks of follow-up).

During the 3-week buffer period for Oura Ring baseline data collection, participants will also complete the following scales on a daily basis:

1. Patient Health Questionnaire - 2 item (PHQ-2; modified for daily administration)
2. Generalized Anxiety Disorder Scale - 2 item (GAD-2; modified for daily administration)
3. Measure of minutes of PA engaged in in the past day

As with the Oura Ring data collection, completion of the daily scales will continue throughout the study for a total of approximately 13 weeks (i.e., during the ~3 weeks of baseline, during the 4 weeks of the intervention period, and during the 6-weeks of follow-up).

Finally, the participant will be randomized into the PA group or TAU group as per Section 2.10. Depending on the outcome of the randomization, participants in the PA group will schedule their five sessions with their assigned trainer (see Section 2.12.1.3).

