### **2.18.3 Collection of AEs**

The condition of the participant will be monitored throughout the study. At each visit, whether scheduled or unscheduled, AEs will be recorded using an Adverse Events Log. In addition, the Principal Investigator and/or the co-investigators will check the participant records for any documented event.

Any AE which occurs during the study will be noted in detail on the appropriate pages of the CRF. If the participant reports several signs or symptoms representing a single syndrome or diagnosis, the diagnosis should be recorded in the CRF. The investigator will grade the severity of all AEs (mild, moderate, or severe), the seriousness (non-serious or serious), and the likelihood that they were related to the PA programme (causality).

Diseases, signs and symptoms, and/or laboratory abnormalities already present before the first administration of the PA programme will not be considered AEs unless an exacerbation in intensity or frequency (worsening) occurs.

The investigator will provide detailed information about any abnormalities and about the nature of and reasons for any action taken as well as any other observations or comments that may be useful for the interpretation and understanding of an AE.

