#### **2.18.5 Causality of AEs**

All AEs will be assessed by a blinded Investigator as to whether they can be explained by the participant's underlying condition. If they are not explainable, then the Investigator will make a determination of the relationship of the AE with the IMP (i.e., the PA programme) as follows:

- **Probable:** reports including good reasons and sufficient documentation to assume a causal relationship, in the sense of plausible, conceivable, likely, but not necessarily highly probable. A reaction that follows a reasonable temporal sequence from administration of the IMP and that could not reasonably be explained by known characteristics of the participant's clinical state.
- **Possible:** reports containing sufficient information to accept the possibility of a causal relationship, in the sense of not impossible and not unlikely, although the connection is uncertain or doubtful, for example because of missing data or insufficient evidence. A reaction that follows a reasonable temporal sequence from administration of the IMP but that could readily have been produced by several other factors.

- **Unlikely:** reports not following a reasonable temporal sequence from administration of the IMP. An event which may have been produced by the participant's clinical state or by environmental factors or other therapies administered.
- **Not related (unrelated):** events for which sufficient information exists to conclude that the etiology is unrelated to the IMP.
- **Unclassified:** reports which for one reason or another are not yet assessable (e.g., because of outstanding information (can only be a temporary assessment)).

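### The adverse-event definition and onset rule cover only participants receiving the PA programme, which contradicts the AE logs required in TAU; the schedule also shows no AE log until week 4

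*Protocol*

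**What the plan says.** **Definition.** Section 2.18.2 opens with "An AE is any untoward medical occurrence in a study participant receiving the PA programme". Its second sentence keeps the same limit, ending with "disease temporally associated with the use of an investigational medical product (IMP), whether or not related to the IMP"; 2.18.5 identifies the IMP as the PA programme.

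**Onset.** Under 2.18.3, conditions "already present before the first administration of the PA programme will not be considered AEs" unless they worsen. The same section asks for AEs to be recorded at every visit, scheduled or not, and for any AE during the study to be noted.

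**Collection.** The note to 2.6.1 says that "the CONMED and AE log will occur during the supervised PA session for participants randomized to the PA group", with a weekly phone call instead for TAU. Section 2.12.1.4 repeats the TAU call, 2.12.5 has weekly AE calls in both groups during follow-up, and 2.12.1.6 lists an AE log at the exit visit without restricting it to one arm.

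**Timing.** Section 2.12.1.3 describes the week-1 baseline visit and closes with "Finally, the participant will be randomized into the PA group or TAU group as per Section 2.10". Ring use starts at that visit, "approximately 3 weeks prior to the start of the intervention period, to establish participants' baseline parameters". The AE row in 2.6.1 has no entry for screening, week 1 or weeks 2-3.

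**Causality.** Section 2.18.5 says "All AEs will be assessed by a blinded Investigator". Section 2.18.3 gives the causality judgement to the investigator without mentioning blinding, and 2.11 names outcome assessors and data analysts as blinded but not those who assess AEs.

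**The concern.** Staff on a weekly TAU call have a log to complete and a definition under which nothing they hear qualifies. They must either ignore the definition or record nothing, and two staff members could choose differently. The restriction carries forward, because severity grading (2.18.4), causality (2.18.5) and one of the discontinuation grounds in 2.3 all use the term AE.

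Section 2.18.1 names cardiac events and musculoskeletal injuries as possible risks, and 2.14.1 says there will be no data safety monitoring committee, so the AE log is a main safeguard. TAU participants receive movement guidelines and are encouraged to be active (2.1), so their events are a useful background rate for reading those in the PA arm. Section 2.13 also wants to keep these data for the final trial, so a one-armed definition could carry over into it.

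**Working it through.** **1. Calendar, reproducing the Protocol's own figure.** From 2.6.1: week 1 (allocation and baseline) plus weeks 2-3 (buffer) = 3 weeks; weeks 4-7 (intervention) = 4; weeks 8-13 (follow-up) = 6. Total 3 + 4 + 6 = 13 weeks, as stated in 1.2.

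**2. Who is covered by the definition.** Section 2.10 states that "20 participants will be randomized to the PA group and 10 participants will be randomized to the TAU group". Under the literal wording of 2.18.2, the excluded share is 10 / 30 = 33%, all of it TAU.

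**3. Definition against collection.**

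| Section | Are TAU events AEs, or logged? |
|---|---|
| 2.18.2 | No: limited to those receiving the programme |
| 2.18.3, pre-existing rule | Cannot be applied: no first administration in TAU |
| 2.6.1 note and 2.12.1.4 | Logged: weekly call, weeks 4-7 |
| 2.12.5 | Logged: weekly calls in follow-up |
| 2.12.1.6 | Logged: exit visit |

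The first two rows cannot be satisfied together with the last three.

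**4. The onset anchor.** For TAU, the rule compares an event with a date that never occurs. Either every event precedes it, or the rule never applies. For PA, the date is ambiguous. Trainer session 1 falls in the buffer and consists of psychoeducation, goal setting and planning; supervised activity starts in week 4 (2.12.1.4). If the first administration means week 4, a problem arising in weeks 1-3 is pre-existing, although the same section wants any AE during the study noted.

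**5. The gap in the schedule.** Randomization is in week 1 and the first AE mark is in week 4, so the lag is 4 - 1 = 3 weeks. Assuming 30 participants with full follow-up:

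- all: 30 × 3 = 90 of 30 × 13 = 390 participant-weeks, 90 / 390 = 23%
- PA: 20 × 3 = 60 of 20 × 13 = 260, 23%
- TAU: 10 × 3 = 30 of 10 × 13 = 130, 23%

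The share is the same in each arm. The baseline visit list in 2.12.1.3 includes the concomitant medication record but no AE log, although grip strength, sit-to-stand and push-up tests are done there.

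**6. Order within the baseline visit.** In 2.12.1.3 the ink consent signature comes first, the fitness tests follow, and randomization is described last. An anchor set at randomization would therefore class an injury from those tests as pre-existing. An anchor set at consent would not.

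**The case against.** The strongest reply is that these are slips of wording with little effect on the data. TAU has weekly AE contacts from week 4 and an AE log at exit. The SAE definition in 2.18.8 carries no arm restriction. Section 2.18.3 already requires recording at every visit and throughout the study. Comparing harms is not a stated aim, and 2.13 rules out comparative analyses on clinical outcomes. Much of this stands, and it rules out several stronger readings that a reader might infer.

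- *That harms cannot be compared or assessed.* Both arms are logged weekly from week 4 to the end, so the records would exist. What fails is the rule for what counts as an AE in TAU, and with it the descriptive control rate.
- *That AE recording is fixed to begin 3 weeks late, and biases the arms.* The blank row conflicts with 2.18.3; it does not override it. The gap is equal in both arms, so by itself it loses early events and does not favour either arm. Session 1 lists no exercise, so the buffer should not be presented as unlogged supervised training.
- *That blinded causality review is impossible.* Section 2.18.5 first asks whether the underlying condition explains the event, which does not need the allocation. Judging temporal relation to the programme is harder without it, but the documents show an inconsistency across 2.11, 2.18.3 and 2.18.5, not an impossibility. Unblinding that investigator is a debatable trade-off and does not follow from the text.

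What the reply does not remove is the literal conflict. The definition, the onset anchor and the collection window are fixed in the Protocol itself, and they disagree.

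**Conclusion.** The point holds as an internal contradiction in the safety rules. Sections 2.18.2 and 2.18.3 state a rule that gives the wrong result for TAU: taken as written, 10 of 30 participants can have neither an AE nor a defined onset, against four places that require their events to be logged. The 33% is the size under the literal reading. It is not a forecast of lost data, since staff may well log TAU events anyway.

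The second part is a conflict between the schedule and 2.18.3 over weeks 1-3, which make up 23% of each participant's 13 weeks. That figure assumes full follow-up and the nominal calendar; the Protocol gives the baseline period only as about 3 weeks. The third part is a disagreement on who is blinded. The change is worth making because it is cheap and improves safety ascertainment, but no feasibility conclusion is shown to depend on it.

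**What to change.** - **2.18.2:** apply the definition to any participant in either arm, from consent to the exit visit, and remove the link to receipt or use of the programme.
- **2.18.3:** replace the first-administration anchor with consent. Randomization should not be used, because the baseline fitness tests precede it. State which consent is meant: 2.12.1.1 has a digital signature before screening and 2.12.1.3 an ink signature at baseline. Both come before the tests.
- **2.6.1:** add an AE entry at the baseline visit, after the fitness tests, and list it in 2.12.1.3. Have the first week-4 log in both arms ask about all events since the baseline visit.
- **2.11, 2.18.3 and 2.18.5:** reconcile them on whether the investigator who judges relatedness is blinded.

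The cost is amendment wording and one schedule entry. No new contact is needed. This matters because TAU has no routine staff contact in weeks 2-3: its weekly calls start in week 4, and the compliance calls in 2.4.6 are made only when data are missing. Adding AE entries in the buffer at existing contacts would therefore reach PA, through session 1, but not reliably TAU. The small downside of the week-4 look-back is recall over about 3 weeks, the same in both arms.

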### **2.18.3 Collection of AEs**

The condition of the participant will be monitored throughout the study. At each visit, whether scheduled or unscheduled, AEs will be recorded using an Adverse Events Log. In addition, the Principal Investigator and/or the co-investigators will check the participant records for any documented event.

Any AE which occurs during the study will be noted in detail on the appropriate pages of the CRF. If the participant reports several signs or symptoms representing a single syndrome or diagnosis, the diagnosis should be recorded in the CRF. The investigator will grade the severity of all AEs (mild, moderate, or severe), the seriousness (non-serious or serious), and the likelihood that they were related to the PA programme (causality).

Diseases, signs and symptoms, and/or laboratory abnormalities already present before the first administration of the PA programme will not be considered AEs unless an exacerbation in intensity or frequency (worsening) occurs.

The investigator will provide detailed information about any abnormalities and about the nature of and reasons for any action taken as well as any other observations or comments that may be useful for the interpretation and understanding of an AE.

#### **2.18.4 Severity of AEs**

The intensity/severity of AEs will be graded as follows:

**Mild:** an AE, usually transient, which causes discomfort but does not interfere with the participant's routine activities.

**Moderate:** an AE which is sufficiently discomforting to interfere with the participant's routine activities.

**Severe:** an AE which is incapacitating and prevents the pursuit of the participant's routine activities.

The grading of an AE is up to the medical judgment of the Investigator and will be decided on a case-by-case basis.

#### **2.18.5 Causality of AEs**

All AEs will be assessed by a blinded Investigator as to whether they can be explained by the participant's underlying condition. If they are not explainable, then the Investigator will make a determination of the relationship of the AE with the IMP (i.e., the PA programme) as follows:

- **Probable:** reports including good reasons and sufficient documentation to assume a causal relationship, in the sense of plausible, conceivable, likely, but not necessarily highly probable. A reaction that follows a reasonable temporal sequence from administration of the IMP and that could not reasonably be explained by known characteristics of the participant's clinical state.
- **Possible:** reports containing sufficient information to accept the possibility of a causal relationship, in the sense of not impossible and not unlikely, although the connection is uncertain or doubtful, for example because of missing data or insufficient evidence. A reaction that follows a reasonable temporal sequence from administration of the IMP but that could readily have been produced by several other factors.

- **Unlikely:** reports not following a reasonable temporal sequence from administration of the IMP. An event which may have been produced by the participant's clinical state or by environmental factors or other therapies administered.
- **Not related (unrelated):** events for which sufficient information exists to conclude that the etiology is unrelated to the IMP.
- **Unclassified:** reports which for one reason or another are not yet assessable (e.g., because of outstanding information (can only be a temporary assessment)).

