### **2.18.9 SAE Reporting Timelines**

Reporting to REB: The study investigator will report all SAEs that are unexpected AND there is a reasonable possibility that the SAE is related to the research study to the REB within 7 calendar days of the study team becoming aware of the event. All fatal or life-threatening SAEs that are unexpected AND there is a reasonable possibility that the SAE is related to the research study will be reported within 3 days. Follow-up reports of the SAE will be submitted to the REB whenever new relevant information regarding the SAE becomes available until the resolution of the SAE.

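### Section 2.18.5 judges relatedness only for AEs the underlying condition cannot explain, while 2.18.3 requires a causality grade for every AE; the two must be reconciled

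*Protocol*

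**What the plan says.** Section 2.18.5 sets out two steps. The first applies to every event: "All AEs will be assessed by a blinded Investigator as to whether they can be explained by the participant's underlying condition". The second is conditional on the first: "If they are not explainable, then the Investigator will make a determination of the relationship of the AE with the IMP". Five categories follow: Probable, Possible, Unlikely, Not related and Unclassified.

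Section 2.18.3 gives a different rule. In one sentence covering all AEs, the investigator grades severity, seriousness and "the likelihood that they were related to the PA programme (causality"). No condition is attached. The same section says that problems already present before the programme starts "will not be considered AEs unless an exacerbation in intensity or frequency (worsening) occurs", so a worsening of the depression being treated is an AE.

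Section 2.18.9 has the investigator "report all SAEs that are unexpected AND there is a reasonable possibility that the SAE is related to the research study". Such reports go to the REB, with a limit of 7 calendar days, or 3 days if the event is fatal or life-threatening.

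**The concern.** Whether an illness could account for an event, and whether the intervention may have contributed to it, are separate questions. Section 2.18.5 lets a yes to the first close off the second. The bar is low, since the test is only whether the condition can explain the event.

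This matters more here than in most trials because the underlying condition is the trial's indication. The psychiatric events that a trial in treatment-resistant depression most needs to evaluate (depressive worsening, self-harm, psychiatric admission) are those the indication most readily explains. An event that closely follows a programme session and one with no link in time to the programme could both stop at the first step, with nothing recorded to tell them apart.

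Two things are at stake: the completeness of the record on whether the programme is related to psychiatric harm, and the basis for the relatedness judgement that REB reporting needs. Formal safeguards are otherwise light, with no data safety monitoring committee (2.14.1), no planned interim analysis (2.14.2) and no pre-specified independent audit (2.19).

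**Working it through.** No arithmetic applies. The check sets the safety sections side by side and follows one event through them.

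**Inputs**

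- Population (2.2.1): a current major depressive episode confirmed by structured interview, and at least two failed antidepressant trials within that episode.
- Numbers (2.10): 30 randomised 2:1, so 20 to the programme and 10 to TAU.
- AE definition (2.18.2): an untoward occurrence in a participant receiving the programme, whether or not causally related.
- Grading rules: 2.18.3 and 2.18.5. Reporting rule: 2.18.9.

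**Step 1: one event, two rules.** Take a depressive worsening in a programme participant.

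| Question | Under 2.18.3 | Under 2.18.5 |
|---|---|---|
| Is it an AE? | Yes, as a worsening | Assumed |
| Is relatedness graded? | Yes, as for all AEs | Only if the depression is judged unable to explain it |
| Does timing relative to the programme count? | It can, within the grade | Not if the event stops at the first step |

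When the investigator judges that the depression can explain the event, 2.18.3 calls for a grade and 2.18.5 does not. Neither section says which prevails.

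**Step 2: the filter against the scale it feeds.** Unlikely includes this: "An event which may have been produced by the participant's clinical state or by environmental factors or other therapies administered". Possible takes in a reaction with reasonable timing "but that could readily have been produced by several other factors". The definition of Probable likewise asks whether the participant's clinical state could reasonably account for the reaction. All three treat competing explanations as something to weigh while grading. The filter treats one such explanation, the underlying condition, as a reason not to grade. If it is applied, events attributed to that condition never reach the category written for events that the clinical state may have produced.

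**Step 3: the default for filtered events.** Section 2.18.5 does not say what is recorded for an event that stops at the first step. The field might be left blank or Not related might be assumed. The second does not fit the scale, because Not related requires enough information to conclude that the cause lies elsewhere. Being explainable by depression falls short of that.

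**Step 4: the link to reporting.** Section 2.18.9 needs a view on whether a relation to the study is reasonably possible. It does not refer to the 2.18.5 categories, so the investigator can and should form that view for any SAE. For an event stopped at the first step, however, no causality determination made under 2.18.5 would support it.

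**The case against.** The strongest reply is that 2.18.3 already requires a causality grade for all AEs, so grading is not absent and the matter is one of wording. This stands in part. A reader might infer from 2.18.5 alone that worsening depression receives no grade at all; 2.18.3 contradicts that, and the defect is a conflict between two rules. The conflict still has practical weight, because 2.18.5 is the section devoted to causality and staff may well follow it over one sentence elsewhere.

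Second, the first step is a judgement made event by event. The investigator may find a given worsening not explainable and go on to the scale. This also stands: such events will often stop at the first step, but nothing makes that automatic.

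Third, a reader might infer that an ungraded event cannot qualify for REB reporting. The text does not support this. Section 2.18.9 sets its own test, refers to the research study and does not depend on a 2.18.5 grade. Section 2.15.1 also has AEs reported to the REB under current guidelines.

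Fourth, a reader might link the word unexpected in 2.18.9 with the statement in 2.18.1 that "Serious inherent risks are rare but include cardiac events and musculoskeletal injuries", and conclude that exercise injuries and cardiac events are exempt from reporting. That is only one possible reading. Section 2.18.1 calls these risks rare and never calls them expected, and 2.18.9 does not define the term by reference to 2.18.1. It is no ground for rewriting the two-part REB criterion.

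Finally, REB reporting is not the only outside check. The participant's most responsible physician is informed of participation (2.8), the participant's doctor may withdraw them (2.3), and institutional representatives, including the REB, may inspect records (2.19).

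**Conclusion.** The concern holds as a contradiction between 2.18.3 and 2.18.5, together with a misfit inside 2.18.5 between its first step and its own categories. If 2.18.5 is followed, depressive worsening, self-harm or psychiatric admission will often not be graded for relatedness. The judgement needed under 2.18.9 would then lack a recorded basis, and programme-related psychiatric events could be under-recorded.

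On size, every one of the 30 planned participants has the condition that triggers the filter. Relatedness to the programme is mainly at issue for the 20 allocated to it. The protocol states no expected AE or SAE rate, so no count of affected events can be given.

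The conclusion assumes that staff would apply 2.18.5 as written, and that investigators would often regard psychiatric events as explainable by the depression. It does not assume that they always would. The passages should be reconciled, but the point does not call the trial's design or primary feasibility outcomes into question.

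**What to change.** In 2.18.5, delete the first-step filter. State that every AE receives one of the five listed causality categories, with the participant's underlying condition as one consideration in choosing it. This brings the section into line with 2.18.3 and lets Possible and Unlikely work as defined. Section 2.18.9 can stay as it is, since a grade would then be on record for every SAE.

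The cost is a sentence or two in an amendment and a few more AEs graded Possible or Unlikely in a 30-person trial. The change affects recording only and leaves participants' treatment as it is.
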